**Fig. 3 Fig3:**
[figure not shown]
Study design showing related variables and confounders

### Kenya as a comparison country

Comparatively, Kenya showed relevant commonalities as Ghana and was chosen as a comparison country. First, Kenya DHS data were collected about the same time as Ghana and had no such intervention within the time frame. This is necessary for the DID analysis.

Secondly, the DHS reports of the two countries show similarities of related variables of interest in this study. For example, Ghana recorded 30 and 50 per 1000 live births for neonatal and infant mortality rates respectively, and within the same period, Kenya also recorded 31 and 52 per 1000 live births for neonatal and infant mortality, according to their respective 2008 DHS reports [59–61].

Also, Kenya was considered appropriate giving its geopolitical and socioeconomic similarities to Ghana such as; political stability, literacy rate, lingua franca, and Sub-Saharan location.

### Data source and size

Ghana and Kenya 2008/2014 DHS data sets are collected about the same time by MEASURE DHS, a USAID sponsored program. DHS used a similar questionnaire of international standards to collect the 2008/2014 data sets, which serves as the main data source for this study. The advantage of using DHS data has been widely documented [62, 63]. DHS collects wide and multipurpose data with a standard questionnaire which includes health indices and contains variables relevant for this current study.

Children data sets, KR data, collected data from women in household settings within their reproductive ages of 15–49 years of both countries will be used for the quantitative analysis. Cross country data analysis will only be required at the stage of the quantitative analysis owing to the DID method.

However, primary data will be collected from one selected region in Ghana, the Upper East Region, based on the odds of coverage of the ‘free’ policy, for an in-depth description of the policy in the real-world setting. This is relevant to add context to the study findings and empower the discussion. Ghana’s data sets are represented by the 2008/2014 GDHS data collected from 12,323/12,831 households respectively using a two-stage sampling technique.

Kenya, on the other hand, is represented by the KDHS data sets of 2008/2014, also collected using two-stage sampling design from a representative household sample of 9936/40,300 from 400 clusters (133 urban, 267 rural) and 1612 clusters (997 rural, and 617 urban) for the 2008/2014 respectively [45, 48].

In total, the sample size of Ghana 2008/2014 DHS data are n = 2992/5884, whereas, those of Kenya are n = 6079/20,964 for the 2008/2014 respectively. The two countries' data sets were collected, approximately 6 years into the implementation of the ‘free’ maternal healthcare policy in Ghana, and considered adequate and representative in size to power the study.

### Sample weighting

Due to the complex nature of the two-stage sampling design, which essentially produces a complex survey data sets, sample weighting will be applied across the data sets, to cater for clustering (the enumeration areas) and stratification (urban/rural area of residence) for precision. Sample weighting will be set in STATA 15 software, using variable *v021* and v022 from the data sets, as primary sampling units and strata respectively. Thereafter, all commands will prefix the svy (survey) to apply sample weighting in the analysis*.*

The choice of rural/urban area of residence allows for socio-economic variation to be incorporated into the data composition and analysis. Hence, robust standard error (Taylor Linearization and bootstrapping) approach will be used to adjust for clustering and stratification bias.

Sample probability weighting will be generated through the selection of sample weighting variable *v005* from the data sets and divided by 1000,000, to cater for the 6 decimal places, usually not reported in Demographic and Health Survey data, thus, stata command of;

*gen wgt* = *v005/100,000,* then, *svyset [pw* = *wgt], psu (v021) strata (v022) to set the DHS data.*

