### Demographic and health survey data

Demographic and Health Survey data sets are a household survey collected using a two-stage sampling method. Clusters for the sampling in Ghana used sampling frames of the 2000 and 2010 population and housing census to sample for the 2008 and 2014 DHS surveys respectively. For 2008, 412 clusters were determined in the first stage. In the second stage, 29 households were selected from each of the 412 clusters. Household from one cluster data was left out due to ethnic conflict at the time, thus 12, 323 households were selected.

The 2014 DHS also determined 427 clusters; 216 urban areas and 211 rural areas. The second stage then sampled 30 households per cluster for questionnaire administration in each household, thus, 12,831 households, similar to the sampling technique for the 2008 DHS.

In both situations, women between the ages of 15 and 49, who were either permanent residents in the selected households or stayed in the household the night before the selection were eligible to participate in the study and had their blood pressure measured. Sampling excluded women living in barracks, hotels, and prisons. Children between 0 and 59 months were also eligible and had their height and weight checked.

Eligible women participated in the study and answered questions on; age, pregnancy status, education, and relationship to the household head, residence, birth history, parity, pregnancy outcomes, knowledge and use of family planning methods, malaria interventions, diarrheal diseases, antenatal care and facility, and facility delivery (children born within the last 5 years).

Whereas GDHS 2008 collected data on the NHIS, the GDHS 2014 collected information on the free maternal health policy. Ghana and Kenya DHS surveys are similar in sampling procedures and methods and therefore comparable. DHS surveys are considered alternative to population and housing census in many situations due to their wide range of coverage in public health and socio-economic variables.

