### Protocol implementation

This protocol will be implemented in phases as per the design. Proposal writing preceded the protocol’s approval and the approved protocol will be implemented as outlined in Table 6 (see Additional file 1). The implementation will also be monitored by the Ghana Health Service Ethics Committee, as well as the supervisory committee of the University of Ghana Public Health School. The approved protocol follows the standard of research required for the award of a doctoral degree set out by the University of Ghana.

**Table 6 Tab6:** Protocol implementation, monitoring & evaluation

Phase I	Phase II	Phase III
*Review of relevant literature on;* Maternal health care policy Maternal health care utilization Burden of stillbirths Perinatal deaths Neonatal mortality *Retrieval of secondary data from MEASURE DHS;* Ghana DHS 2008 Ghana DHS 2014 Kenya DHS 2008 and Kenya DHS 2014 *Cleaning and organization of DHS data:* Dropping of irrelevant variables Merger of data sets *Variable management* recoding and renaming *Preliminary analysis of DHS data (secondary data)* Hypothesis testing Analysis of association and Determination of significant levels (set at ≤ 0.5)	Gaining entrée for primary data collection *Primary data collection* In-depth interviews (IDIs) of service providers Focus Group Discussion (FGD) among pregnant women *Preliminary analysis of qualitative data* Data transcription Annotation of significant statement Coding and Categorization of common themes *Key Informant Interviews* Transcription of key informant interviews *Triangulation of data* Drawing congruence of policy user Perspective/perception, Service provider perspective and Policy implementers view points	*Presentation of preliminary findings and feedback at;* Institutional level Clinical forum ANC clinic to policy users *Summary presentation at;* Regional Annual Performance Review *Presentation of final report at;* School of Public Health, University of Ghana *Publication of Final report for policy actors, research and scientific community in;* MOH reports NHIA report Internal journals Local journals Policy briefs
Monitoring and evaluation of phase I, II, and III		
Guidance and comments of Co-investigator 1,2 and 3	Guidance and comments of Co-investigators 1 and 2	Scheduling of presentation Purview of Co-investigators and faculty of Health Policy Planning Management of the University of Ghana Public Health School

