### Data analysis

The secondary data will be cleaned and organized, dropping irrelevant variables and renaming covariates for ease of reference as necessary. Essentially, variables of interest in this study are binary outcomes i.e. 1 = case/the presents of an intervention, and 0 = no case, the absence of intervention, control.

Both multivariate logistic regression and Poisson with robust standard error, or negative binomial regression depending on whether there is over dispersion (conditional variance exceeding the conditional mean) will be fitted and analyzed. Thus, **loge** {*p*1 / *(1—pi)*} = *b0* + *b1 Xi1* + *b2 Xi2* + … + *bkXik*. The Use of the multiple logistic regression model also comes with the advantage of adjusting for confounding by including the covariates in the model.

For the matching method, Ghana’s DHS data sets (2008 and 2014) will be merged. This will increase the sample size to n = 8876, and add power to the study. The merger will also eliminate the risk of lack of common support, the so-called curse of dimensionality, a common phenomenon in propensity score matching, where treated units propensity scores cannot find suitable pairs.

Descriptive data will be presented using tables, frequencies, and proportions. The data will then be analyzed distinctly, using multiple statistical models and quasi-experimental design techniques. Firstly, the student independent *t*-test will be used to test for proportions, the significance of association, and mean differences between the independent variable, and the binary outcomes of interest; antenatal care uptake, and facility delivery utilization.

Test of association set < 0.05 less of significance, between the secondary variables of interest (stillbirth, perinatal death, and neonatal mortality) and the covariates; mothers age, marital status, level of education, wealth index, region, area of residence, twin delivery, parity, and employment status will be determined by using the Rao Scot Chis-square, which has an added sensitivity advantage, while adjusting for complex survey design features (weighting, clustering and stratification).

Only covariates found to be significantly associated with the dependent or independent variables will then be included in a multiple logistic regression model and adjusted for confounding [72].

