Logistics regression is considered appropriate, giving the binary status variables of interest; antenatal care up-take [yes = 1 (ANC visit ≥ 4)] and [no = 0 (ANC visit of ≤ 3]; facility delivery utilization [yes = 1 (facility delivery) and no = 0 (home delivery)], and the secondary outcome variables; stillbirth, perinatal and neonatal deaths, generated through the re-coding of the relevant variable *m14, m15, b6, b7*, and *s1015,* from the DHS data sets (Table 5).

The treatment difference will be determined through nearest-neighbor matching of treated and untreated units’ propensity scores generated ex-post, and using logistics regression while controlling for the confounding variables for precision. The 'free' policy impact will then be determined using the average treatment effect on the treated. Robustness of results will be achieved with reduced standard errors using bootstrapping replication while testing for sensitivity using a t-test of bias, and probit regression.

Of the treatment and comparison country analysis, the DID analysis will be used to determine the policy impact, using the 2008 data set of the two countries (Ghana and Kenya) as a baseline and 2014 data sets as the end line. The study is powered by the sample size calculation, originally determined by the survey design. The sample size is n = 2992/5884 (8,876) for Ghana DHS 2008/2014 data sets, and n = 6079/20,964 (27,043) for Kenya DHS 2008/2014 data sets respectively.

Clustering and stratification will be adjusted for using sample survey weighting at all stages of the analysis. This will produce unbiased treatment estimate that can be generalized to the original survey population [26, 52].

The qualitative data will be deductively analyzed using predefined themes. However, common themes that emerges from the interviews and focused discussion will be organized as sub-themes and inductively reported. The approach will be aided by NVIVO 12, through which nodes and their children will be created to categories significant statements into similarities and dissimilarities [73].

The results of the primary data will be reported using the common themes approach with word frequency count and cloud, and vivid quotations to back themes. The inclusion of qualitative data will add context and situate the discussion with explanatory power to the statistical findings [48].

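### The printed svyset line carries no survey identifier, so on the merged Ghana 2008 and 2014 file it treats strata of independent surveys as one, and standard errors can err in either direction

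*Protocol article*

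**What the plan says.** All references are to the protocol article.

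- **Sample weighting** takes v021 and "v022 from the data sets, as primary sampling units and strata respectively", describes the stratification as "stratification (urban/rural area of residence", and prints a command ending "psu (v021) strata (v022) to set the DHS data". After that, "all commands will prefix the svy (survey) to apply sample weighting in the analysis".
- **Data analysis** states, for the matching method, that Ghana's "DHS data sets (2008 and 2014) will be merged", giving n = 8876. **Statistical methods and rationale** also announces a merger of the 2008 and 2014 data for matching.
- **Data analysis** describes the difference-in-differences (DID) as "using the 2008 data set of the two countries (Ghana and Kenya) as a baseline and 2014 data sets as the end line".
- **Protocol implementation**, Table 6, lists "Merger of data sets" after retrieval of all four surveys, without saying which sets are merged.
- **Demographic and health survey data** says that the Ghana rounds used "sampling frames of the 2000 and 2010 population and housing census", so the two sets of clusters come from different frames.

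No section adds a country or round identifier to the PSU or stratum variable.

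**The concern.** Each survey round is an independent sample. In a stacked file its strata must be kept apart from those of the other rounds, and so must its clusters. A stratum variable that only says urban or rural takes the same two values in every survey. The printed command would therefore tell Stata that Ghana 2008 rural clusters and Ghana 2014 rural clusters are draws from one stratum. If v021 is numbered afresh in each survey, clusters that share a stratum and a number would also be read as one cluster.

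The article relies on this setup to handle clustering and stratification throughout. Any svy-based standard error, confidence interval or test computed on a merged file inherits the misspecification. A standard error that is too small makes false significance at p < 0.05 more likely. One that is too large gives away the precision that the weighting section says stratification is there to protect.

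**Working it through.** **1. The article's own figures.** Ghana: 2992 + 5884 = 8876. Kenya: 6079 + 20,964 = 27,043. Both match. The article states no standard error, design effect or design degrees of freedom (df), so there is nothing further of its own to reproduce.

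**2. Strata and clusters.** Cluster counts come from the article: Ghana 2008, 412 less the one left out = 411; Ghana 2014, 427; Kenya 2008, 400; Kenya 2014, 1612 (its urban and rural counts add to 997 + 617 = 1614; the stated total is used). Design df = PSUs − strata.

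| File | Codes | Strata | PSUs | Design df |
|---|---|---|---|---|
| Ghana merge | survey-unique | 2 × 2 = 4 | 411 + 427 = 838 | 834 |
| Ghana merge | raw | 2 | about 612–647 | about 610–645 |
| Four surveys, if pooled | survey-unique | 2 × 4 = 8 | 838 + 400 + 1612 = 2850 | 2842 |
| Four surveys, if pooled | raw | 2 | about 1952–1982 | about 1950–1980 |

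The strata column follows from the article's urban/rural description. The raw PSU and df figures also assume that cluster numbers restart at 1 in each survey. They fall only part of the way because Stata nests PSUs within strata, so clusters merge only when both codes match. The loss of df is harmless in itself: the two-sided 5% critical value is about 1.964 at 610 df and 1.963 at 834 df.

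**3. How the variance is affected.** The linearised variance is

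V = Σ_h [n_h/(n_h − 1)] Σ_i (z_hi − z̄_h)²,

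where z_hi is the total of linearised scores in PSU i of stratum h. For a contrast of proportions between rounds, with equal weights, a woman in round r has score ±(y − p_r)/n_r. These scores sum to zero within each survey, so differences in survey means do not enter V. Two other things do:

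- *Shared strata.* If urban residence raises the outcome, urban clusters score positive in one round and negative in the other. In one shared urban stratum the mean is near zero, so the urban/rural difference that stratification should remove stays in V. The standard error rises.
- *Shared PSUs.* Totals of opposite sign are added before squaring. If same-numbered clusters resemble each other, for example because numbering follows region, they cancel. The standard error falls.

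**4. Size.** Binary outcomes were simulated on the counts above with equal weights. Assumptions, none of them from the article: Ghana 2008 is 44% urban; cluster SD 0.5–1.0, region SD 0–1.2 and urban effect 0–1.5 on the logit scale; cluster numbers random or ordered by region. Ratio of the raw-code standard error to the correct one:

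- Ghana 2008–2014 contrast: 0.87 to 1.11
- Four-survey DID: 0.90 to 1.14

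Some DID settings, all with cluster SD 0.5:

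| Region SD | Numbering | Urban effect | Raw strata and PSUs | Raw strata, unique PSUs |
|---|---|---|---|---|
| 0 | random | 0 | 0.996 | 0.999 |
| 0 | random | 1.5 | 1.144 | 1.259 |
| 1.2 | by region | 0 | 0.902 | 0.999 |
| 1.2 | by region | 1.5 | 0.958 | 1.078 |

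The last column is the case in which cluster codes happen not to repeat: only the upward effect remains. With unique strata and raw PSU codes the ratio was 1.00, because the nesting then keeps the clusters apart.

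**5. Meaning for a 5% test (normal approximation).** At a ratio of 0.87, the nominal 1.96 becomes 1.96 × 0.87 = 1.705, a true error rate of about 8.8%. At 1.14 it becomes 1.96 × 1.14 = 2.234, about 2.5%, and the effective sample is 1/1.14² = 0.77 of what it should be.

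**The case against.** The strongest reply is that this is a condensed article. Unique identifiers are ordinary data management, Table 6 lists recoding after the merger, and no sentence says that svyset is run on the merged file. This would settle the matter if the article had left the design setup open. It did not: it prints the command, names the raw variables and applies the result to everything that follows.

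Other objections stand and limit the point.

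- **Cluster codes are not shown.** Only the overlap of strata follows from the article. The overlap of PSUs is conditional.
- **A pooled Ghana–Kenya file is not stated.** Table 2 defines the DID from four cell values, which could be estimated from four surveys set up separately; the problem would then not arise. The merge is explicit only for Ghana.
- **The explicit merge serves matching**, for which Data analysis names bootstrap standard errors. The svyset line then matters only through any svy step on that file, and through which clusters a bootstrap resamples. The article does not say that the Rao-Scott tests use merged data.
- **Adjustment would probably shrink the effect.** Residence and region are listed as covariates, and the simulated contrast was unadjusted.

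A reader might go further and infer standard errors that are always too large, by as much as 1.49 times, from assuming finer strata (for example 20 in Ghana and 16 in Kenya). Those counts are not in the article, which describes urban/rural strata; on that description the error has no fixed direction. A reader might also infer that differences between surveys inflate the variance of the contrast. Step 3 of the working shows that they drop out.

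**Conclusion.** The point holds in a limited form. Applied to the merged Ghana file, the printed command misstates the design: 2 strata where there are 4 independent ones. It would give 2 in place of 8 if all four surveys were stacked. Whether clusters are also conflated depends on coding that the article does not show.

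Point estimates are unaffected. Svy-based standard errors, intervals and tests on merged data can be too small or too large, roughly 0.87 to 1.14 times the correct value if cluster numbers restart, and close to 1.00 without an urban/rural effect and with numbering unrelated to geography. This range illustrates the assumed effects and is not a bound: with raw strata but unique cluster codes, one DID setting reached 1.26. The documents do not support saying that the standard errors are certainly wrong, or wrong in a known direction. It is a modest fault in stated code, worth correcting because the correction is so cheap.

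**What to change.** Before svyset on any merged file, create identifiers that are unique to each survey:

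`egen psu_u = group(country year v021)`

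`egen str_u = group(country year v022)`

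`svyset psu_u [pw=wgt], strata(str_u)`

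Here country and year are constant within each source file and are added before stacking; year means the survey round, not the calendar year of interview. Use psu_u and str_u in any bootstrap that resamples clusters. State in the plan which files are merged for the DID, or that its four cells are estimated from separately declared surveys.

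The cost is two lines of code and a sentence of text. If the codes are already unique, the results do not change.

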### Statistical methods and rationale

The design and intentions of the ‘free’ policy could not allow for randomization, the gold standard for impact evaluation, hence, quasi-experimental methods; DID and PSM techniques are adopted for the analysis of the secondary data sets. These methods are considered appropriate in evaluating public health programs that have no randomization in the policy design and implementation stages, and in particular, suitable for policies whose choice of participation is somewhat open and voluntary.

Combining the two methods gives the advantage of one making up for the limitations posed by the other. The DID analysis will employ the 2008 data sets of the two countries as baseline data (the starting time), whereas the 2014 DHS data sets of the same will represent the end line (the end time), as shown in Table 2.

**Table 2 Tab2:** Difference-in-differences method

	Before treatment	After treatment	Difference
Treatment (T)	X_0_	Y_0_	T = Y_0_–X_0_
Comparison (C)	X_1_	Y_1_	C = Y_1_–X_1_
Difference	X_0_–X_1_	Y_0_–Y_1_	DD = (Y_0_–X_0_) – (Y_1_–X_1_) = T-C

The choice of propensity score matching technique is also appropriate for the estimation of the policy average treatment effect through the generation of comparators ex-post. A drawback of PSM is the risk of lack of common support for paring treated units to the untreated. This particularly occurs when the sample size is small, so-called the curse of dimensionality. However, this study will merge the 2008/2014 data sets to increase the sample size and to minimize the risk of the curse of dimensionality [49].

Increased sample size will also enhance the study power for precision, albeit, also determined in the original two-stage DHS sampling design. The combined effect of the two quasi-techniques will eliminate the limitation of one and enhance the robustness of the study results [64, 65].

From Table 2 above, before treatment (baseline) is represented be GDHS 2008 (X_0_) for the treatment, T, and KDHS 2008 (X_1_) for the comparison group, C. The after treatment (end line) is also represented by Y_0_ and Y_1_ for Ghana DHS 2014 and Kenya DHS 2014, respectively. Thus, the DID analysis is the difference of T = (y_0_–x_0_) and C = (y_1_–x_1_); estimate for the before treatment difference and the after-treatment difference. The differences between the two represent the treatment effect, thus, the treatment effect is = (y_0_–*x*_*0*_) − (y_1_–*x*_1_), which is equal to T-C.

